## Abstract

**Background:**

The low utilisation of current treatment services by people with gambling problems highlights the need to explore new modalities of delivering treatment interventions. This protocol presents the design of a pragmatic randomized control trial aimed at assessing the effectiveness and acceptability of cognitive behavioral therapy (CBT) delivered via a mobile app for people with self-reported gambling problems.

**Methods:**

An innovative CBT mobile app, based on Deakin University’s GamblingLess online program, has been adapted with end-users (Manaaki). Six intervention modules have been created. These are interwoven with visual themes to represent a journey of recovery and include attributes such as avatars, videos, and animations to support end-user engagement. An audio facility is used throughout the app to cater for different learning styles. Personalizing the app has been accomplished by using greetings in the participant’s language and their name (e.g. Kia ora Tāne) and by creating personalized feedback.

A pragmatic, randomized control two-arm single-blind trial, will be conducted in New Zealand. We aim to recruit 284 individuals. Eligible participants are ≥18 years old, seeking help for their gambling, have access to a smartphone capable of downloading an app, able to understand the English language and are willing to provide follow-up information at scheduled time points. Allocation is 1:1, stratified by ethnicity, gender, and gambling symptom severity based on the Gambling Symptom Assessment Scale (G-SAS). The intervention group will receive the full mobile cognitive behavioural programme and the waitlist group will receive a simple app that counts down the time left before they have access to the full app and the links to the data collection tools. Data collection for both groups are: baseline, 4-, 8-, and 12-weeks post-randomisation. The primary outcome is a change in G-SAS scores. Secondary measures include changes in gambling urges, frequency, expenditure, and readiness to change. Indices of app engagement, utilisation and acceptability will be collected throughout the delivery of the intervention.

**Discussion:**

If effective, this study will contribute to the improvement of health outcomes for people experiencing gambling problems and have great potential to reach population groups who do not readily engage with current treatment services.

**Ethics approval:**

NZ Health and Disability Ethics Committee (Ref: 19/STH/204)

**Trial registration:**

Australian New Zealand Clinical Trial Registry (ANZCTRN 12619001605189) Registered 1 November 2019.

## Background

Internationally, standardised prevalence rates of problem gambling range from 0.5 to 7.6%, with an average rate across all countries of 2.3% [1]. In New Zealand, the prevalence of people with some level of risk for gambling problems is estimated at 6.8% of the population, whereby approximately 0.3% of the population experience problem gambling with a further 1.5% classified with moderate-risk gambling and 5.0% with low-risk gambling [2]. Māori (indigenous people in New Zealand) and Pacific peoples have higher rates of all levels of gambling risk and have more persistent gambling problems over time [3, 4]. The negative sequelae of gambling problems can include financial harm, relationship dysfunction and conflict, emotional distress, health decrements, cultural harm, reduced work or study performance, and criminal activity [5].

### Treatment approaches to problem gambling

Traditionally, individuals seeking help for gambling-related issues have obtained treatment from general physicians or specialised counselling services through face-to-face sessions. Treatment approaches that use cognitive behavioural therapy (CBT) appear to help reduce gambling activity and related behaviours in the short term [6]. Motivational interviewing (MI) strategies also provide benefit by reducing aspects of gambling behaviour, such as cutting back or reducing the amount of money gambled [7, 8]. Nevertheless, fewer than 10% of people with a gambling problem are in face-to-face treatment at any one time [2, 9], with most seeking treatment only in response to a significant life crisis [10]. Reasons and barriers for the lack of face-to-face uptake include cost, geographical distance, transport limitations, conflicting commitments, fears of stigmatisation and shame, and privacy concerns [11, 12]. New approaches are therefore needed to enhance access to address gambling-related harm.

Internet-delivered interventions have grown over the past decade and respond to many of the barriers reported as being responsible for the low uptake of face-to-face services [13, 14]. Nonetheless, few studies have evaluated self-directed gambling interventions delivered over the internet. A recent systematic review revealed that the two available high-intensity, self-directed, structured, online gambling interventions [15, 16] were as effective on all outcomes following treatment compared to those obtained from face-to-face treatments [17]. Since then, an online self-directed CBT program (GamblingLess) has been developed by some of the researchers for the proposed trial. The program was developed as a comprehensive and intense intervention that emulates the intensity and depth of a face-to-face cognitive-behavioural intervention, and from which briefer and more targeted online and app-based self-directed interventions can be developed. A recent pragmatic randomised trial in Australia examined the programme delivered without any practitioner (clinician) guidance or delivered with practitioner guidance at 8-weeks, 12-weeks, and 24 months from the pre-intervention assessment (Dowling N, Merkouris S, Rodda S, Smith D, Lavis T, Lubman D, et al. GamblingLess: For Life: A pragmatic randomised trial of an online cognitive-behavioural program for disordered gambling. *in preparation*, [18–20]). They found statistically significant improvements in gambling symptom severity, gambling urges, gambling frequency, gambling expenditure, and psychological distress within both treatment groups across the evaluation period. There were also significant improvements in quality of life for the guided self-directed group. At the end of the 24-month evaluation period, 69% of the sample were recovered or improved on gambling symptom severity. The programme was also positively evaluated by both end-users and guides. However, further controlled studies are needed to conclusively confirm the efficacy of this intervention.

### Mobile health (mHealth): a new opportunity for problem gambling

The technological capability of smartphones is opening up new ways to consider providing intervention and relapse prevention support [21]. Mobile health (mHealth) interventions, which include texting, self- directed activity and sensors within (e.g. step counter) or tethered to, mobile phones (smartwatch) to address health issues across the continuum, have great potential for public health impact because of their broad reach and convenience [22].

Smartphone apps have been shown to support self-management and behaviour change for smoking cessation [23], cardiac rehabilitation [24], healthy lifestyle [25], diabetes [26], HIV [27], nutrition [28], mental illness [29] and youth driving [30]. In a recent meta-analysis of smartphone interventions for mental health problems, smartphone apps outperformed waitlist controls with small to medium effect sizes [31]. The effect size was greater for apps that had a theoretical basis in CBT. Apps that were compared with active control were not found to be significantly different.

The use of mobile apps remains largely untapped in the gambling domain [32]. Our previous work, SPGeTTI, an application that utilised innovative technology including GPS and notifications to support gambling relapse prevention reported positive participant engagement during the formative development phase [33]. Despite technical and recruitment challenges, participants in the study reported an ongoing interest in having smartphone apps as potential tools to support them to quit or reduce their harmful gambling [34]. Other mHealth studies have also reported similar positive engagement and acceptability with smartphone apps [35, 36].

Concurrent with the growth in mHealth tools is the exponential growth in smartphone ownership internationally and in New Zealand [37]. A Pew Research Report also highlights that the age gap in smartphone ownership is also narrowing [38]. Globally, the use of the advanced features available on mobile phones surpasses the use of basic features such as text messaging [39]. In New Zealand, a 2014 survey reported that smartphone ownership was more common among Māori and Pacific people (70%) than Europeans (55%) [40]. In addition, 92% of New Zealand households have access to a mobile phone [41], with no differences in internet access or smartphone ownership by ethnicity or education, or age [41]. Thus, there is considerable potential in New Zealand to leverage mHealth technology in addressing gambling-related problems.

## Rationale for research

The low utilisation of current treatment services by people with gambling problems highlights the need to explore new modalities of delivering treatment interventions to reach those groups who prefer to self-manage and may prefer not to access (or remain in) face-to-face services. The positive results from internet-delivered gambling intervention programmes are important, as is the emerging evidence that interventions delivered using mobile phones have the potential to reach a wide group of people experiencing gambling problems. The early gambling research into mHealth indicates that these modalities are acceptable and feasible. The combination of high smartphone ownership and demand for health apps provide both the opportunity and vehicle to reach a significant portion of the population who may not readily engage with current health or treatment services.

## Objective

The primary aim of the study is to evaluate the effectiveness of a smartphone application intervention for people with self-reported gambling problems. Specifically, we hypothesize that compared with a wait-list control, the use of a self-directed and personalized CBT based app [Manaaki] for 12 weeks post-randomization will lead to:
Reduction in gambling symptom severity (primary outcome)Reduction in gambling urges, gambling frequency, gambling time and gambling expenditure and improved readiness, willingness, and ability to change (secondary outcomes)

A secondary aim is to explore app engagement, utilization and acceptability.

## Methods

### Design

This study is a pragmatic, randomised, wait-list controlled, single-blinded, two-arm trial. Eligible individuals will be randomly allocated to the Manaaki app (intervention group) or the waitlist control group. Data will be obtained from all participants at baseline, then at 4-, 8-, and 12-weeks post-randomisation. The study has been approved by the New Zealand Health and Disability Ethics Committee (Ref 19STH204) and any changes will be reported as per ethics standard operating procedures and policies. The study is also registered with the Australian New Zealand Clinical Trial Registry (ACTRN12619001605189p), and the protocol conforms to the SPIRIT statement [42].

### Participants

A total of 284 individuals residing in New Zealand will be recruited. Individuals will be eligible for inclusion in the study if they are aged 18 years and over, have an interest in seeking help for their own gambling, have access to a smartphone capable of downloading an app, have access to the internet, possess adequate knowledge of the English language and are willing to provide follow-up information at scheduled time points. Individuals who indicate that they do not meet the inclusion criteria will be ineligible and unable to complete the process to activate the app. As this is a pragmatic study, accessing other help or treatment services is not an exclusion criterion.

### Data safety monitoring and auditing

This study does not meet the requirements for a data safety monitoring committee and as such one has not been established. The study will be audited prior to recruitment initiated.

### Setting

This study will be conducted nationwide in New Zealand. Methods to recruit individuals will include media advertising, peer referral and promotion through appropriate networks, relevant agencies, community groups and peer networks. Media advertising channels will include print media and online advertisements (including websites such as TradeMe, Facebook and Google Adwords) and radio. Recruitment will also be promoted via links to health-specific websites. Networks through our study partners, Hāpai Te Hauora, who facilitate the national coordination service for minimising gambling harm, will also be utilised.

### Study procedures

Figure 1 shows the study procedure. Interested participants will download the app from either the App Store or Google Play. The study participant information will be presented to them. If they have questions, the study contact details are included in the information section of the app, and participants have an opportunity to talk and ask questions with a researcher about the study before deciding to participate. Participants who wish to participate will be presented with a summary of what participation means (i.e. what they are agreeing to) and they can either provide their electronic consent (e-consent) or decline. If a person does not wish to participate, they can select - decline. A thank you for considering participating in the Manaaki study will be displayed. Validation criteria will be utilised where practicably possible; for example, downloading can only be completed by individuals within NZ by placing a location boundary restriction on the app in the App stores, and if month and year of birth entered indicates that the participant is under 18 years, then a “thank you but you are not eligible” pop-up message will appear. Consent to collect app use data from all participants after their 12-week study period is complete will also be sought.

**Fig. 1 Fig1:**
[figure not shown]
Manaaki Enrolment Pathway

Following e-consent, participants will be guided through the baseline data collection questions, which include the criteria for randomisation (ethnicity, sex and G-SAS 0–30 or 31–48). Once all baseline questions completed, participants will be randomised to the Manaaki intervention app or the waitlist control app. To prevent participants who are randomised to the Waitlist control app from uninstalling and reinstalling the app in a desire to receive the Manaaki intervention app, the unique phone ID will be used to confirm an existing login. The waitlist participants will be able to access the full app at the completion of the 12-week study period.

All data collection assessments (baseline, 4, 8 and 12-weeks) will be embedded within the app. A koha (gift) of NZ$60 will be provided to each participant in the form of a grocery voucher. The koha will be divided into three equal amounts of NZ$20 and administered at the completion of each follow-up data point.

All data is housed on a password protected secure server. Access to the final data set will be to the study statistician and appropriately approved study researchers.

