### Study intervention

#### Manaaki app

Participants randomized into the intervention group will have full access to the Manaaki app. The content of the app was adapted from GamblingLess, an online CBT program evaluated in an Australian pragmatic trial (Dowling N, Merkouris S, Rodda S, Smith D, Lavis T, Lubman D, et al. GamblingLess: For Life: A pragmatic randomised trial of an online cognitive-behavioural program for disordered gambling. *in preparation*, [19]). The program incorporates content related to motivational enhancement, cognitive and behavioural strategies, and relapse prevention strategies. Formative work has been conducted to enhance the tailoring of content and develop content that was deemed culturally relevant and appropriate for New Zealand users. The program was also redeveloped as an interactive application that can be used on a mobile phone. Table 1 details the modules, conceptual framework, and intervention elements of the Manaaki app.

**Table 1 Tab1:** Domains and intervention elements for the programme

Modules	Conceptual Framework	Underpinning Intent	Key Intervention Elements
Knowing Myself (and my gambling)	Developing self-awareness and insight [44]	Designed to provide personalised feedback, goal setting, and understanding of gambling motivations, triggers, and/or consequences	Personalised feedback on gambling symptom severity and gambling behaviour Reflecting on their goal of quitting or cutting back reasons for gambling My gambling triggers My negative gambling consequences My reasons for gambling
Getting Ready (to make changes)	Targeting thoughts and feelings and activating behaviours [46]	Designed to enhance readiness and confidence to gamble less, helping to shape thoughts and values to help make change	Am I ready to gamble less? Knowing my values Knowing my strengths The benefits of gambling less My confidence Deciding on my goal for change
Taking Control (right now)	Targeting practical behaviours and identification of situational and contextual triggers	Designed to identify strategies that can be used to “contain” the gambling in the short-term, directs to other useful tools such as venue exclusions	My previous strategies to gambles less Limiting access to venues Limiting access to money Guidelines for gambling safely Resisting social pressures

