#### Waitlist control app

Participants randomized to the waitlist control group will have access to the waitlist app which presents a timer that shows participants the days remaining until they are able to activate the full intervention app (Fig. 2), the data collection forms and links to available gambling services. Participants will receive short push notifications (messages) reminding them to complete data collection at 4-, 8-, and 12-weeks and their importance in taking part in the trial. At the end of the 12-week period, upon completion of the final data collection, participants will have full access to the Manaaki app.

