#### Primary outcome

The primary outcome is a change in G-SAS at 12 weeks. The G-SAS consists of 12 items designed to assess change in gambling symptom severity during treatment. It uses a past week timeframe with each item scored from 0 to 4, with varying response options for each item. Total scores on the G-SAS range from 0 to 48, with higher scores indicating greater gambling symptom severity. Scores on the G-SAS are categorised as extreme (41–48), severe (31–40), moderate (21–30), or mild (8–20). The G-SAS has demonstrated high internal consistency and good convergent validity with other measures of gambling symptom severity [50].

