The clinical significance of any effect will be demonstrated by calculating effect sizes presented as Cohen’s d for continuous and normally distributed primary and secondary outcomes. Because Cohen’s d effect sizes are based on the assumption of normality for continuous data, odds ratios (ORs) and CIs will be employed as a measure of effect size for ordinal and categorical outcomes. A clinically significant change, as outlined by Jacobson and Truax [60], will also be evaluated for G-SAS gambling symptom severity. At each evaluation, each participant’s status will be defined as “recovered” (final score falls into the functional range and corresponds to a reliable change), “improved” (final score corresponds to a reliable change, but falls into the dysfunctional range), “unchanged” (final score does not correspond to a reliable change), or “deteriorated” (final score corresponds to a reliable change in the negative direction). On the G-SAS, the functional range is defined as scores falling in the mild range or below (i.e., score of 20 or less).

Missing data will be managed based on the following: 1) follow-up of all randomised individuals will be attempted, using notification prompts through the app and where agreed, via the contact details provided at consent. As the data is captured electronically, the project manager will be able to view who has completed, who has not, and what set of reminder notifications are sent (the research team and statistician will not have access to allocation or any study data), 2) for data collection time points at 4-, 8- and 12-weeks, a two-week timeframe will be allowed for each follow-up assessment. Response intervals and frequency of questionnaire completion will be expected to vary between individuals. The two-week period post due date was selected as reasonable, as all participants will receive a notification 1 week before each data collection time point indicating that they can complete that questionnaire, and 3) if a participant misses a timeframe to contribute to a specific data point, it does not preclude them from completing the next data evaluation point.

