## Limitations

This study has potential limitations. First, it is possible that unforeseen technical issues may present barriers to delivering the intervention content. The research team has extensive experience in developing and delivering mhealth interventions and, with an in-house technical team, will work closely to monitor and resolve any technical issues throughout the study period using the appropriate mobile app crash and other technical issue reporting tools. The app will also be pre-tested and have an initial soft launch prior to the full promotion and launch of the full trial. Second, low engagement has commonly been reported in mobile app intervention studies. To ensure that the intervention is appealing and engaging for participants, we developed the app in consultation with people with lived experience of problem gambling and providers of gambling treatment services. Specific attention has been paid to the end-user interface, including graphics, colour, tone, and language. Aspects such as avatars and other strategies for personalizing the app to the user have been incorporated to support app “stickiness” and support participant retention. Thirdly, the presence of the waitlist app used in the control group may have a Hawthorne effect on the findings [61]. To mitigate this, the waitlist app has been designed as a simple placeholder and data collection tool, that has a timer to indicate when the full app will be available. From an ethical viewpoint, it is unethical to completely withhold treatment/intervention for individuals who seek gambling help or support and as such participants in the control group are able to seek any help that they wish during the study period. Finally, the use of a waitlist control group does impact on the ability to measure the effects of the intervention app in the longer term.

Despite these limitations, access and uptake of existing services for gambling problems remain low, and there is a need to explore new approaches to deliver support and treatment for individuals experiencing gambling problems. mHealth offers a promising approach by removing many barriers related to reach and access by high need populations. This has the potential to increase impact at a population level and go some ways to reducing inequality. Information on uptake and adherence to this type of intervention will also be generated to inform future studies for individuals with gambling problems.

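### As described, the 12-week G-SAS can be answered only inside the app, so uninstalling Manaaki ends treatment and outcome collection together, and loss of the primary outcome may differ by arm

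*Protocol article*

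**What the plan says.** - **Where outcomes are collected** (Study procedures): "All data collection assessments (baseline, 4, 8 and 12-weeks) will be embedded within the app". This covers the primary endpoint (Primary outcome): "The primary outcome is a change in G-SAS at 12 weeks".
- **What the app is in the intervention arm** (Manaaki app): "Participants randomized into the intervention group will have full access to the Manaaki app". The treatment and the outcome form share one vehicle.
- **Chasing non-responders** (Data analyses): "follow-up of all randomised individuals will be attempted, using notification prompts through the app and where agreed, via the contact details provided at consent". A two-week window applies, and missing one time point does not bar the next. No web, telephone or postal version of the questionnaire is described.
- **Reasons to stay.** In the waitlist arm (Waitlist control app): "At the end of the 12-week period, upon completion of the final data collection, participants will have full access to the Manaaki app". In both arms (Study procedures): "The koha will be divided into three equal amounts of NZ$20 and administered at the completion of each follow-up data point".
- **Missing data** (Data analyses). The primary analysis is intention-to-treat (ITT) with last value carried forward (LOCF). Per-protocol, complete-case and multiple-imputation analyses are sensitivity analyses.
- **Expected loss.** The Sample size calculation allows 40% attrition, drawn as a worst case from a cited range of 14 to 50%. The Limitations section acknowledges that "low engagement has commonly been reported in mobile app intervention studies".

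**The concern.** An ITT comparison needs outcomes from people who stop treatment as well as from those who continue. Here one act, deleting the app, removes the treatment, the reminder and the form. Someone reached through contact details would, as the article describes things, have to reinstall the treatment in order to report on it.

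The arms are not alike in this respect. Deleting the waitlist app also removes the form, but it stops no treatment. Waitlist participants also have a reward for completing week 12 that intervention participants, who already hold the full app, do not. The NZ$20 payments are equal in both arms and do not offset this. Missing 12-week scores may therefore differ between arms in number and in cause. Inflating the sample for 40% attrition protects power but does not protect against that.

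**Working it through.** **1. The plan's own figure.** The article gives no standard deviation (SD), so SD = 10 is inferred. Per arm, n = 2 × (1.960 + 1.282)² × SD² / 5².
- SD 10 gives 84.1, so 85 evaluable per arm. Then 85 / (1 − 0.40) = 141.7, so 142 per arm and 284 in total. This matches.
- SD 8, 9 and 12 would give totals of 180, 230 and 408.

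The 40% is therefore an allowance for lost numbers. It assumes nothing about who is lost.

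**2. Inputs for an illustration.** The article gives no expected changes by arm or by use of the app, so these are assumptions:
- app arm, stayers: G-SAS falls S = 8
- app arm, people who uninstall: falls T = 3
- waitlist: falls W = 3
- share lost in the app arm: a = 0.40 (the plan's attrition rate, here all treated as uninstallers)
- share lost in the waitlist arm: w, varied, with loss unrelated to outcome

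**3. True ITT difference** = (1 − a)S + aT − W = 0.6 × 8 + 0.4 × 3 − 3 = **3.0**.

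**4. Complete case** (a sensitivity analysis) = S − W = 8 − 3 = **5.0**. The excess over the truth is 2.0 points. In general it is a × (S − T) = 5a, which is 0.7 at 14% loss, 2.0 at 40% and 2.5 at 50%.

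**5. LOCF** (the primary analysis), with baseline carried forward for those lost = (1 − a)S − (1 − w)W.
- Waitlist fully observed (w = 0): 0.6 × 8 − 3 = **1.8**, which is 1.2 points too low.
- Both arms lose 40%: 0.6 × 8 − 0.6 × 3 = **3.0**, equal to the truth.

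The LOCF error is wW − aT. With T = W = 3 it is 3 × (w − a), so it vanishes when loss is equal and changes sign with the arm that loses more.

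**6. Different assumptions.** Let everyone improve 5 points regardless of treatment and let stayers gain a further 5 (S = 10, T = W = 5).

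| Loss, app / waitlist | True ITT | LOCF | Complete case |
|---|---|---|---|
| 40% / 40% | 3.0 | 3.0 | 5.0 |
| 50% / 30% | 2.5 | 1.5 | 5.0 |
| 50% / 14% | 2.5 | 0.7 | 5.0 |
| 30% / 50% | 3.5 | 4.5 | 5.0 |

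**7. What recovering outcomes does** (step 2 inputs, waitlist fully observed).
- Half of the uninstallers answer: complete case (0.6 × 8 + 0.2 × 3) / 0.8 − 3 = 3.75; LOCF 0.6 × 8 + 0.2 × 3 − 3 = 2.4.
- All of them answer: both give 3.0.

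Both analyses move towards the truth, from opposite sides.

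**The case against.** Several stronger readings are tempting, and the article does not support them.

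- **That the trial will overstate the effect, by 67% in the illustration (5.0 against 3.0).** That is the complete-case result. The primary analysis is LOCF, and the same inputs give it 1.8 or 3.0. Week-4 or week-8 scores may also be there to carry forward, which the illustration ignores.
- **That stopping treatment and leaving the study are the same act.** Only uninstalling has that effect. The modules are optional and can be taken in any order. A participant can ignore them, keep the app, answer the forms and collect each payment. Low engagement means low use, and the article gives no rate of uninstalling. Treating all 40% attrition as uninstallers is an assumption.
- **That no analysis could repair the loss.** In the illustration, stoppers change exactly as the waitlist does, so imputing them from the control arm returns 0.6 × 8 + 0.4 × 3 − 3 = 3.0. Multiple imputation is planned, its model is not shown, and app-use data could inform it. But whether stoppers resemble the waitlist cannot be checked without their outcomes.
- **That contact details will be used only for prompting.** The article does not limit them in that way, and a condensed article may leave non-responder procedures to the full protocol. The phone-ID check may also let a reinstalled app be matched to its login.

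These points remove any claim about direction or size. They do not remove the structural link: the article places every assessment in the app, makes off-app contact optional and describes no other form.

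**Conclusion.** The point holds as a weakness of design. In the intervention arm, uninstalling ties loss of the primary outcome to stopping treatment. In the waitlist arm it does not, and there a reward favours staying. Missing 12-week scores can therefore differ between arms in rate and in reason.

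No bias figure follows from the document. Under the assumed changes, a true difference of 3.0 appears as 5.0 in the complete-case analysis and as 1.8 to 3.0 under LOCF as waitlist loss goes from none to 40%. If the waitlist loses more than the app arm, LOCF errs upwards. The practical risk is that the primary and sensitivity analyses disagree and no collected data can settle which is nearer the truth. Because the remedy is cheap and uncollected outcomes cannot be retrieved later, the change is worth making.

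**What to change.** Keep the in-app forms and add the following:

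1. For anyone in either arm who has not answered by the due date, or has uninstalled, and who gave contact details, send the same 4-, 8- or 12-week questionnaire as a personal web link by text or email. Use the same two-week window and the same payment.
2. State in the protocol and the participant information that stopping or uninstalling the app is not withdrawal from follow-up.
3. Record the mode of completion for each questionnaire.
4. Encourage participants to give a contact route at e-consent, but do not require it. The Background lists stigma, shame and privacy among the barriers to seeking help, so a compulsory contact could deter the people the trial wants to reach.

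The cost is a web copy of a short questionnaire and a wording amendment. The downside is a mixed mode of completion, which item 3 makes visible. People who give no contact details and uninstall will still be lost, so the change reduces the problem without removing it.
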